### Statistical power and analysis

We plan to enroll 68 individuals with a biopsy-proven diagnosis of IBD, aged 18 years or older, who meet criteria for impaired IBD-related quality of life and report recent abdominal pain or bowel symptoms, with the aim of a final sample of 50 study participants, assuming 25% attrition during the 5-week study period. A 9-point change in SIBDQ score is considered clinically meaningful and corresponds to a standardized effect size of 1.0 SD [35, 58, 59]. This proposed sample of 50 participants (25 participants in the morning light treatment group and 25 participants in the TAU group) provides ≥ 80% power to detect a clinically meaningful change in our primary outcome measure (SIBDQ) with a two-tailed alpha of 0.05.

We will conduct an intention-to-treat and completer analyses. We will report descriptive statistics of the data by each assessment time (pre-treatment, post-treatment) using appropriate summary statistics. We will analyze both primary and secondary outcomes using a mixed-effects longitudinal data model with participants as random intercepts to account for between participant variability. Predictors will include a post-randomization time indicator, intervention group indicator, and the interaction of time by group. We will examine the extent and pattern of key missing outcomes data and if missingness is greater than 15%, we will assess for baseline characteristics predictive of missingness post-randomization and will include those baseline characteristics as covariates in the final model. While clinician-rated disease activity will be examined as a continuous variable, we will also examine the proportion of participants who show clinical response and/or clinical remission as a binary variable using a generalized linear mixed model with logit link. Clinical response is defined as a decrease in SCCAI score ≥ 3 or a decrease in HBI score ≥ 3. Clinical remission is defined as an SCCAI score of ≤ 2 or an HBI score of < 5.^40,41^

We will explore steroid use, severity of RLS, and biological sex as potential moderators of any treatment effects. We will also perform subgroup analyses to explore differences in responses to morning light treatment between participants with CD versus UC/IBD-unclassified to inform future studies.

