### Outcome measures

Study outcomes will be assessed in both groups at pre-treatment (visit 3) and post-treatment (visit 7). The study assessment schedule is shown **in** Table 3.

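### With two outcome visits, the planned random-intercept model tests mean change and leaves the baseline difference free; using the visit 3 value would usually be more precise at no cost

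*Protocol article*

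**What the plan says.** Outcome measures gives two measurement times: "Study outcomes will be assessed in both groups at pre-treatment (visit 3) and post-treatment (visit 7"). Procedures and assessments places randomisation at visit 3, after the pre-treatment assessments.

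Statistical power and analysis fixes the model for primary and secondary outcomes: it is fitted "using a mixed-effects longitudinal data model with participants as random intercepts", and the predictors are a post-randomisation time indicator, a group indicator and their interaction. Baseline characteristics enter only if missingness exceeds 15%, and only those that predict it. Both an intention-to-treat and a completer analysis are planned.

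The same section gives the power basis. "A 9-point change in SIBDQ score is considered clinically meaningful and corresponds to a standardized effect size of 1.0 SD". The analysed sample is "25 participants in the morning light treatment group and 25 participants in the TAU group", out of 68 enrolled, "with the aim of a final sample of 50 study participants, assuming 25% attrition during the 5-week study period". This "provides ≥ 80% power to detect a clinically meaningful change in our primary outcome measure (SIBDQ") "with a two-tailed alpha of 0.05". The article does not say whether the 1.0 SD is that of a single score or of the change, and it gives no correlation between the two visits.

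Randomization and blinding minimises allocation on SIBDQ (≤ 45 vs > 45), age and sex, and stratifies by Crohn's disease vs ulcerative colitis.

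**The concern.** With two visits, a random intercept and a free group effect, the time-by-group term in complete data is the difference between arms in mean change. That subtracts the baseline with a fixed slope of 1, whatever the actual correlation. The group term spends information on a baseline difference whose expectation is zero, because visit 3 is measured before allocation. Chance imbalance at visit 3 therefore adds noise to the estimate that a baseline-adjusted model would mostly remove.

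What is at stake is precision in a trial expecting 50 completers. The same model serves the secondary outcomes. The Background cites medium effects of light treatment on mood and sleep, where lost precision matters more than at an effect of 1.0 SD. If the 1.0 SD belongs to a single score, the power of the planned test also depends on a correlation the article does not state.

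**Working it through.** **Inputs.** From Statistical power and analysis: 9 points = 1.0 SD, so SD = 9; 25 per arm analysed; 68 enrolled; two-sided alpha 0.05. Assumed: the correlation ρ between visits 3 and 7, equal variances at the two visits, and, for intention-to-treat, 34 randomised per arm (68/2). Enrolment is at visit 2 and randomisation a week later. If some leave in that week, the intention-to-treat results lie between the two cases below.

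**1. The plan's own figure.** Two-sample comparison, 25 per arm, difference 9, SD 9: power 93.4% (noncentral t, 48 df) or 94.2% (normal). The claim of at least 80% is met.

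**2. What the model tests.** In one simulated complete data set (25 per arm, ρ = 0.5), the planned model gave an interaction of 9.136 (SE 2.216). The simple difference in mean change was 9.136 (SE 2.216). ANCOVA on the same data gave SE 1.862.

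**3. Variance, completers.** Per participant, change has variance 2(1−ρ)SD² and ANCOVA has (1−ρ²)SD². The ratio is (1−ρ²)/[2(1−ρ)] = (1+ρ)/2.

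**4. Variance, intention-to-treat.** With n = 25 completing of N = 34, the per-arm variance of the planned contrast is SD²[(1−ρ²)/n + (1−ρ)²/N]. With a common baseline mean only the first term remains. At ρ = 0.5: 0.75/25 = 0.0300 and 0.25/34 = 0.0074, so the ratio is 0.0300/0.0374 = 0.80.

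**5. Effect of minimisation.** Assume a normal baseline, the cut at 45 near the median, and exact balance. The baseline variance within each half is then (1−2/π) = 0.363 of the total, and the completer ratio becomes (1−ρ²)/[(1−ρ²) + 0.363(1−ρ)²]. At ρ = 0.5: 0.75/(0.75 + 0.091) = 0.89.

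| ρ | Completers | Intention-to-treat, 34 per arm | Completers, allowing for minimisation |
|---|---|---|---|
| 0.3 | 0.65 | 0.72 | 0.84 |
| 0.5 | 0.75 | 0.80 | 0.89 |
| 0.7 | 0.85 | 0.89 | 0.94 |

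The last column is actual sampling variance. The planned model omits the SIBDQ category, so its reported SE would not show that benefit.

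**6. Power for 9 points if 9 is a single-score SD.** Change SD = 9√[2(1−ρ)]; ANCOVA SD = 9√(1−ρ²). Completer figures use noncentral t; intention-to-treat figures use the normal approximation with the step 4 variance. Minimisation is ignored.

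| ρ | Planned, completers | Planned, intention-to-treat | Baseline-adjusted, completers |
|---|---|---|---|
| 0 | 68.8% | 76.5% | 93.4% |
| 0.1 | 73.3% | 80.2% | 93.6% |
| 0.2 | 78.2% | 84.0% | 94.2% |
| 0.3 | 83.3% | 88.0% | 95.2% |
| 0.5 | 93.4% | 95.5% | 97.9% |

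The planned test reaches 80% from ρ of about 0.24 among completers (change SD at most 11.1) and from about 0.1 under intention-to-treat.

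**7. Power if 9 is the SD of change.** The planned test has 93% power whatever ρ is.

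**The case against.** The strongest reply is that the planned model is standard, unbiased under randomisation, and used in a trial meant to give preliminary data for a later confirmatory one. That stands, and it makes this a point about efficiency, not validity.

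Three stronger readings are tempting, and the article supports none of them.

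- **That the trial is underpowered.** The stated figure reproduces with room to spare. A shortfall needs the 1.0 SD to be a single-score SD and a correlation below about 0.24 for completers, or about 0.1 for the intention-to-treat model, which also uses dropouts' visit 3 values. The article establishes neither condition.
- **That the random intercept misleads because it assumes equal variances while entry requires SIBDQ < 60.** Table 3 places the SIBDQ at screening and again at visit 3. On that schedule the cut acts on the screening score, not directly on the analysed baseline. With complete data, the interaction and its SE are those of the paired differences even when the visit variances differ.
- **That the planned test is always less precise.** For completers the loss is (SD_pre − ρ·SD_post)². It cannot be negative but can vanish, for example at ρ = 0.7 with SD_post/SD_pre = 1.43. The tabulated ratios need equal variances.

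Two further objections stand in part. Minimisation on SIBDQ category already removes some of the imbalance that adjustment would address. ANCOVA alone would drop randomised participants without visit 7, whom the mixed model keeps, and a single baseline mean for disease activity would mix HBI and SCCAI, which are different scales. These shape the remedy; they do not remove the advantage of using the baseline.

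**Conclusion.** The point holds as one of efficiency. For completers the planned interaction is a comparison of mean change, and the free group term estimates a quantity whose expectation is zero by design. With equal variances, using the visit 3 value cuts the variance by 15% to 35% for completers over ρ = 0.7 to 0.3, and by about 11% to 28% when 34 baselines per arm are used. Allowing for minimisation with the cut near the median, the true completer gain is about 6% to 16%. The correlations, the equal variances and the median cut are assumptions, since the article gives no figures for them.

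The power claim of at least 80% is not refuted. What is missing is a statement of which SD and, if it is a single-score SD, which correlation it rests on.

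**What to change.** - **SIBDQ, PHQ-9 and PROMIS Sleep Disturbance:** drop the group main effect, giving a constrained longitudinal model with a common baseline mean, time, time-by-group and an unstructured 2×2 covariance. Participants without visit 7 stay in.
- **Completer analysis:** ANCOVA of the visit 7 value on arm and the visit 3 value.
- **Disease activity:** adjust for the baseline score within each scale (HBI or SCCAI). Do not impose one common baseline mean across the two.
- **Power statement:** say whether 1.0 SD refers to a single score or to change, give the assumed correlation where it matters, and tie the figure to the contrast that will be tested.

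The cost is a change of analysis wording, best made before any unblinded analysis. No extra patients, visits or data are needed, and the sample size need not change.

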### Randomization and blinding

Participants will be randomized at visit 3 to either 4 weeks of morning light treatment or 4 weeks of TAU in a 1:1 ratio using a minimization approach to reduce imbalances in important covariates including SIBDQ score (≤ 45 vs. > 45 to reflect moderately and severely impaired IBD–related quality of life), age 18–45 years vs. > 45 years, and sex. We will also stratify randomization by CD vs. UC and aim to enroll equal numbers of CD vs. UC and male vs. female participants. Study research assistants assessing outcomes and the clinicians assessing disease activity at study visits 3 and 7 will be blinded to treatment assignment and will be instructed not to discuss any aspect of the treatment with participants. These blinded staff will also wear badges instructing participants to not discuss the study treatment with them. Otherwise, unblinded study staff will meet with participants weekly to download data from the wrist monitor and Re-timer® device (in the light treatment group), provide feedback on adherence, and assess treatment side effects.

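### None of the allocation factors, and not baseline SIBDQ, is a covariate in the stated primary model, so the test is mildly conservative and gives up precision

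*Protocol article*

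**What the plan says.** Under Randomization and blinding, participants are allocated 1:1 "using a minimization approach to reduce imbalances in important covariates including SIBDQ score" (cut at 45), age (18–45 versus over 45) and sex. The same paragraph adds: "We will also stratify randomization by CD vs. UC".

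Under Statistical power and analysis, primary and secondary outcomes go into a "mixed-effects longitudinal data model with participants as random intercepts to account for between participant variability". The predictors are then listed: "Predictors will include a post-randomization time indicator, intervention group indicator, and the interaction of time by group". None of the four allocation factors is named. Other baseline variables can enter only by the missing-data rule. If more than 15% of key outcome data are missing, the analysts look for characteristics that predict missingness and "will include those baseline characteristics as covariates in the final model".

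Outcomes are measured twice, at visit 3 and visit 7 (Outcome measures). Visit 3 SIBDQ is thus a response in the model, not a covariate.

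**The concern.** Balancing allocation on a factor makes the arms more alike on it than simple randomisation would. If that factor predicts the quantity being compared, the treatment estimate varies less from trial to trial. A model that leaves the factor out does not know this. Its standard error still allows for chance imbalance that the design has largely removed, so confidence intervals are too wide and p-values too large.

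The usual remedy of adding the factors as main effects would not help here. With two visits and a random intercept, the time-by-group contrast is a within-person difference, and time-constant terms cancel from it.

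What is at stake is precision in a trial that expects 50 completers. The article itself describes the balanced variables as important covariates.

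**Working it through.** **Inputs from the document.** 68 enrolled, 25% attrition, 25 analysed per arm; 9 points = 1.0 SD, so SD = 9; "with a two-tailed alpha of 0.05"; two visits; the predictors as listed.

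**Assumed, not in the document.** Pre-post correlation ρ of 0.3–0.7; biased-coin minimisation with probability 0.8; how strongly age, sex and disease type relate to outcome; random dropout.

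**1. The plan's own figure.** For a 9-point difference with SD 9 and 25 per arm, SE = 9 × √(2/25) = 2.55. Power is 0.942 (normal) or 0.934 (noncentral t). The stated figure of at least 80% holds.

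**2. What the listed model tests.** On one simulated data set of 25 complete pairs per arm, the mixed model gave a time-by-group estimate of 1.540 (SE 1.819). The change-score comparison gave the same. Adding a baseline factor as a main effect left both unchanged. With incomplete pairs the equivalence is only approximate.

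**3. Which factors matter.** An effect that is equal at both visits cancels; only a relation to *change* inflates the SE. Baseline SIBDQ always has one when ρ < 1, by regression to the mean. With equal variances it explains (1 − ρ)/2 of the variance in change: 0.35, 0.25 and 0.15 at ρ = 0.3, 0.5 and 0.7. Allocation balances only the split at 45, so the share actually balanced is smaller.

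**4. Bound under perfect balance.** If balanced factors explain a share R² of the variance in change, the real type I error is 2 × [1 − Φ(1.96/√(1 − R²))].

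| R² with change | Type I error |
|---|---|
| 0.02 | 4.8% |
| 0.05 | 4.4% |
| 0.10 | 3.9% |
| 0.15 | 3.4% |
| 0.25 | 2.4% |

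**5. Simulated type I error.** 68 randomised by minimisation within disease stratum, 3,000 trials per scenario (simulation SE about √(0.04 × 0.96/3000) = 0.4 percentage points). Age, sex and disease type explain 0 or 10% of change. The SIBDQ used for allocation correlates 0.7 or 1.0 with the visit 3 value.

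| | No dropout | 25% dropout |
|---|---|---|
| Listed contrast, null rejection | 3.1–4.5% | 3.5–4.9% |
| Mean model SE / true SD of estimate | 1.04–1.11 | 1.01–1.07 |

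Adjusting the change score for all four factors gave 4.2–5.7%, nominal within simulation error.

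Other runs of similar set-ups at 25% dropout:
- Factor effects stable across visits (0–30% of variance, ρ = 0.5): 3.4–4.0%.
- No effect of age, sex or disease type: 3.1%, 3.6% and 4.2% at ρ = 0.3, 0.5 and 0.7.
- Stable effects, or at most 10% of residual variance explained: about 3.6–5.2%.
- 30% of residual follow-up variance explained: about 2.0–3.6%.

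**6. Precision.** The SE of the change contrast is 9√(2(1 − ρ)) × √(2/25). Adjusted for baseline it is 9√(1 − ρ²) × √(2/25). Their ratio is √(2/(1 + ρ)): 1.24, 1.15 and 1.08 at ρ = 0.3, 0.5 and 0.7. At ρ = 0.5 the two SEs are 2.55 and 2.20.

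For an illustrative 6-point difference at ρ = 0.5, power is Φ(6/2.55 − 1.96) = 0.65 for the change contrast and Φ(6/2.20 − 1.96) = 0.78 with baseline adjustment. Simulation with 25 per arm and no dropout agrees: 0.66–0.67 and 0.77–0.78. Adding the other three factors gives 0.76–0.88, so they contribute nothing unless they predict follow-up beyond baseline. With 25% attrition the figures are about 0.58–0.65 as listed and 0.68–0.89 adjusted.

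**The case against.** The strongest reply is that little is at risk. The error is conservative, so no false positives arise. The plan targets 9 points, where the listed contrast already has power of about 0.93; the 6-point figure is only an illustration. Stable effects of age, sex and disease type cancel from a within-person contrast, and visit 3 SIBDQ is already in the model as a response. At 25% expected attrition the 15% missingness trigger would probably be met, so some factors may enter anyway. Finally, this is a condensed article, its predictor list is not declared exhaustive, and a separate analysis plan may add covariates.

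Much of this stands, and it limits the size of the point. It does not remove it:

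- Having the baseline as a response, with a free group term, fixes its slope at 1. That is a change score, not an adjustment.
- The missingness rule picks covariates because they predict dropout, not because they were balanced. Entered as main effects, they leave the contrast unchanged in complete pairs.
- The article does not leave the model to another document. It states one, and that model does not reflect the stated allocation.

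A reader might go further and infer that the real type I error falls well below 5%. The document does not support this. A rate near 1.7% appears only if age, sex and disease type explain 30% of the follow-up variance left after baseline, in exactly 25 balanced patients per arm with no attrition. The article gives no such share, and calling a covariate important does not say that it predicts four-week change.

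**Conclusion.** The point holds as a moderate loss of efficiency, not as an error that threatens validity. None of the four allocation factors is a covariate in the stated model, and baseline SIBDQ enters only as a response.

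At the planned attrition the test is mildly conservative: about 3.5–5% null rejection under weak or stable factor effects, with some runs slightly lower (3.1% at ρ = 0.3). It is lower still only if the factors strongly predict change. The SE exceeds the true SD by about 1–7% in the main simulation.

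The more useful gain is precision, and most of it comes from continuous baseline SIBDQ. Its size rests on the assumed pre-post correlation and is smaller as that correlation rises. It would be wrong to say that all precision from the allocation is lost: the point estimate keeps the balance, and what is lost is an SE that reflects it.

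**What to change.** Specify the primary contrast as visit 7 SIBDQ compared between arms, adjusted for continuous baseline SIBDQ, disease type (CD versus UC/IBD-unclassified), sex and age group. An ANCOVA does this directly. If the mixed model is kept, each factor must enter with its interaction with time, because main effects alone leave the contrast unchanged. Since visit 3 SIBDQ is already a response in that model, the text should say how baseline adjustment is achieved, for example by giving both arms a common visit 3 mean.

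Use the same set for the continuous secondary outcomes, with each outcome's own baseline. Where HBI and SCCAI are analysed separately, disease type is constant within each scale and drops out. Keep the missingness rule as an addition to this fixed set, not as the only route by which covariates enter.

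The cost is one sentence of analysis text and three to four degrees of freedom: three for disease type, sex and age group, four with baseline SIBDQ. All these variables are already collected. Naming them now also avoids a data-driven choice later.

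### The 15% missing-data rule will almost certainly fire at the planned 25% attrition, so dropout data would pick the primary model's covariates, with no covariate-by-time term named

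*Protocol article*

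**What the plan says.** All of this is in the Protocol article, mostly under Statistical power and analysis.

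- Size: "We plan to enroll 68 individuals with a biopsy-proven diagnosis of IBD", "with the aim of a final sample of 50 study participants, assuming 25% attrition during the 5-week study period".
- Model, for primary and secondary outcomes: a mixed model with a random intercept per participant. "Predictors will include a post-randomization time indicator, intervention group indicator, and the interaction of time by group".
- Missing data: when more than 15% of key outcome data are missing, "we will assess for baseline characteristics predictive of missingness post-randomization and will include those baseline characteristics as covariates in the final model". The text gives no candidate list or selection criterion, and does not say how the covariates enter the model.
- Outcome times (Outcome measures): one assessment before treatment (visit 3) and one after (visit 7).
- Allocation (Randomization and blinding): "in a 1:1 ratio using a minimization approach to reduce imbalances in important covariates", namely SIBDQ category, age group and sex, with stratification by disease type. The listed model terms include none of these.

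**The concern.** Two things follow from reading these sentences together.

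First, a rule written as a contingency is the expected primary analysis, because the trigger lies well below the planned attrition. The final covariates would depend on which baseline measures happen to separate about 17 or 18 dropouts from the rest.

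Second, the remedy may not reach the bias it is meant for. The treatment effect is the time-by-group term in a two-visit model. A baseline covariate that is constant over time cancels from each completer's change score. Added as a main effect, it acts only through the visit 3 scores of people who lack visit 7. Dropout related to change calls for the covariate's interaction with time, or for an analysis of visit 7 conditional on baseline.

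At stake is a dropout adjustment that is reported as made but may do little. Dropout that differs by arm is possible here: the light arm has a fixed wake time and an hour of treatment on each of 28 days, while TAU keeps its usual sleep.

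**Working it through.** **1. The plan's own figures.** Enrolment: 50 / (1 - 0.25) = 66.7, so 67; the plan states 68, which agrees. Implied loss: (68 - 50) / 68 = 26.5%. SD: "A 9-point change in SIBDQ score is considered clinically meaningful and corresponds to a standardized effect size of 1.0 SD", so SD = 9. With "25 participants in the morning light treatment group and 25 participants in the TAU group", t-test power for 9 points is 93.4%, which meets the stated minimum of 80%. The sample size is not in question.

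**2. Will the rule fire?** 15% of 68 is 10.2, so it fires at 11 or more missing. With X ~ Binomial(68, p), P(X >= 11) is:

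| True missing rate p | Chance of firing |
|---|---|
| 15% | 44.4% |
| 20% | 82.6% |
| 25% | 97.1% |
| 26.5% | 98.4% |

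Enrolment is at visit 2 and randomization at visit 3, so some losses may come before randomization. If 9 of the 18 planned losses do, 9/59 = 15.3% remain and the rule still fires. It takes 10 (8/58 = 13.8%) to avoid it.

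**3. Selection.** Assume 10 candidates unrelated to dropout, each screened at p < 0.05. At least one enters by chance with probability 1 - 0.95^10 = 40%. In a null simulation (3,000 runs) the type I error of time-by-group was 4.5% both with and without this selection.

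**4. What a main effect leaves.** Assumptions not in the protocol: one binary baseline characteristic X coded -0.5/+0.5, split evenly; true effect 9; pre/post correlation 0.3 to 0.7; dropout of 5% and 45% by X in the light arm and 25% for all in TAU. SD is 9.

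Hand check when X shifts visit 7 by 9 points and visit 3 not at all: mean X among light-arm completers is 0.5 x (0.55 - 0.95) / (0.55 + 0.95) = -0.133, and among TAU completers 0. Bias without the covariate is 9 x (-0.133) = -1.2 points. Large-sample fits of the random-intercept model (400,000 subjects) give:

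| X acts on | No covariate | Main effect | With X-by-time | Share left by main effect |
|---|---|---|---|---|
| Visit 7 only (9) | -1.2 | -0.82 to -1.01 | about 0 | 69-85% |
| Visit 3 by 4.5, visit 7 by 9 | -0.77 to -0.98 | -0.43 to -0.53 | about 0 | 44-68% |
| Both visits by 9 | -0.29 to -0.68 | about 0 | about 0 | 1-2% |
| Treatment effect only | -1.2 | -1.04 to -1.13 | -0.65 | 86-94% |

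If dropout depends on X alike in both arms and X does not modify the effect, there is no bias to remove.

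A separate simulation, again with dropout depending on the trait only in the light arm, gives 70-88%, 35-58% and about 0-10% left for the first three patterns. The middle case moves with how strongly the trait acts on visit 3.

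**5. At trial size.** Assumptions: 34 per arm, true effect 4.5, about 25% missing, SD 9, correlation 0.5, a trait acting on visit 7 only and on dropout only in the light arm; 500 trials per scenario, four scenarios. Mean estimates were 5.13-5.82 with no covariate, 5.01-5.56 with a main effect, 4.48-4.56 with the time interaction, and 4.52-4.57 with ANCOVA including the trait (Monte Carlo SE 0.10-0.13).

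**The case against.** The strongest reply has five parts.

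- *The article never says main effects.* This stands. It says only that the characteristics become covariates. A reader might infer that the protocol prescribes main effects and so leaves most dropout bias in place; the text does not support that as fact. What can be said is that the listed terms contain no covariate-by-time term.
- *The bias claim depends on the scenario.* This also stands. The share left runs from almost none to most. Because the likelihood fit also uses dropouts' visit 3 scores, the contrast is not purely within-person, and a main effect does remove bias from a trait that shifts both visits equally. Measures such as PHQ-9 probably track baseline SIBDQ too, so the visit-7-only case is the extreme one.
- *The bias is small.* In these scenarios it is about 1.2 points at most before adjustment in the large-sample runs, against a 9-point meaningful change and a standard error near 9 x sqrt(2/25) = 2.5. This limits the severity.
- *Selection on missingness has not been shown to inflate false positives.* Correct. A reader might infer inflation from data-driven covariates, but the null simulation shows none.
- *A rule stated in advance is still pre-specified, and 25% is only a sample-size allowance.* True: 15% beside 25% is not a contradiction. But the rule fixes a procedure and not a model, and at the planned attrition the procedure will run.

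Differential dropout is also unproven: the trial excludes people who cannot fit the light session into their morning, contacts both arms daily, and stopping light is not the same as missing visit 7.

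**Conclusion.** The point holds in a limited form. At 25% attrition the rule fires with probability about 97%, so covariates chosen from the trial's own dropout become part of the primary model. That conclusion needs only the protocol's figures and a binomial count.

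The second part is conditional. If the covariates enter as main effects only, and dropout depends on a characteristic differently by arm, the time-by-group contrast is not properly adjusted for dropout related to change. Under SD 9 and correlation 0.3 to 0.7, about 70-88% of the bias stays if the characteristic acts on visit 7 only, about 35-58% if it acts on both visits but more on visit 7, and almost none if it acts equally on both. The documents do not support a general statement that the rule leaves most of the bias, nor one that it inflates type I error. The change is worth making because it is cheap and no worse in any scenario examined.

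**What to change.** Drop the 15% trigger. Name a short covariate list now from data already collected: baseline SIBDQ, disease type, sex and age, which are the allocation factors, plus at most one or two expected predictors of both dropout and outcome, such as baseline PHQ-9. Include them whatever the missingness, in one of two ways:

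- ANCOVA on visit 7 SIBDQ with these as covariates; or
- the planned longitudinal model with each covariate's interaction with time. Visit 3 SIBDQ is already a response in that model, so it needs no separate term.

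Move predictors of missingness found in the data to a sensitivity analysis.

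Cost: wording and a few degrees of freedom. In ANCOVA on 50 completers, five or six one-degree covariates reduce the residual degrees of freedom from 48 to 43 or 42. One limit remains: if a characteristic modifies the treatment effect, its interaction with time removes only part of the bias (0.65 of 1.2 points left above), and removing the rest needs a term with group as well.
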